## Post-intervention (Stage Two participants only)

Teacher: Conners Teacher Ratings

Estimate of treatment group

Child: Reading test age

Working memory digit span test

Fingerprick blood measures to assess compliance

Estimate of treatment group

The following measures will be collected from parents using Freepost mail services and chased up with telephone calls or visits as required.

Parent: Conners Parent Ratings

Estimate of treatment group

Child Sleep Habits Questionnaire (CSHQ)

Barkley Side Effects Rating Scale (SERS) (Barkley, 1990)

On the same selected subsample, we will again collect sleep measures objectively by actigraphy and derive the CSDI from the sleep diary.

Participants in both stages of the study will be given a 3 month supply of DHA (Life’s DHA, provided by Martek Biosciences Corporation) as a token of thanks for their participation in the study.

In due course, the parents of all participating children will also receive details of the overall study results, as will all participating schools.

# ASSESSMENTS AND PROCEDURES (2) – Details of measures

## Screening

### Key Stage 1 Reading score

Key Stage tests are nationally standardized assessments taken by all UK children at ages 7, 11 and 14. They encompass five areas: speaking and listening, reading, writing, science and mathematics.

Reading scores from Key Stage 1 tests will be used to screen for children performing in the lowest third for their age against national norms at age 7. To be eligible for the study, children must be judged by teachers to be performing normally in at least one other domain.

## Baseline and post-intervention

### Conners Teacher and Parent Ratings (CTRS-L and CPRS-L)

These are standardized highly valid and reliable scales which measure child behaviour over several domains, yielding age-standardised scores for 7 different sub-scales (6 for teacher ratings) and 7 global scales.

These scales have shown significant improvements following fatty acid supplementation in several previous trials, and have been routinely used in medication trials for children with behaviour problems such as ADHD.

Teacher ratings will be the primary outcome measure in both Stage One and Stage Two as this is a school-based study, but every effort will be made to ensure that parents also complete ratings pre- and post-treatment. By taking measures from both parents and children at Stage Two we will be able to assess whether any changes in behaviour can be seen in different situations.

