## Outcome Measures

With respect to behaviour, clinical rating scales are rarely sensitive enough to detect treatment effects, and neither these nor various computer tests designed to assess attention or impulsivity have proved successful to date (Voigt *et al*, 2001; Stevens *et al* 2003; Hirayama*, et al.*, 2004). In this study, behaviour will be assessed by both teachers and parents, using well-validated questionnaire rating scales that are (a) psychometrically sound, (b) suitable for general population use and (c) likely to be sensitive to any treatment effects. The Conners’ Scales (Conners 1997) were originally developed to assess pharmacological treatments for child behaviour problems, and have shown benefits in three of the successful RCTs of omega-3 for child behaviour and learning ([name] & Puri, 2002; [name] & [name], 2005; Sinn & Bryan 2006)

With respect to cognitive function, simple, transparent measures are again likely to be the most useful. The Oxford-Durham study showed clear benefits from fatty acid treatment for literacy skills (reading and spelling), and also on a simple, widely used test of working memory. Age-standardised tests of reading performance and working memory will therefore be used as primary outcomes in this study.

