## Primary Endpoint

1. To confirm or refute that supplementation with Omega-3 fatty acids (DHA, 600mg/day) for 16 weeks improves behaviour and learning in children aged 7 – 9 years from mainstream schools who are underperforming academically.

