### Primary outcome

- Can supplementation with Omega 3 (DHA) improve child behaviour and learning in underachieving children aged 7-9 years? Outcomes assessed will include reading performance, working memory and ADHD-type symptoms (inattention, hyperactivity, impulsivity) as rated by teachers and parents.

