## Sample Size

At Stage One, our previous studies indicate that a sample of 600 participants will be needed to identify an adequate number of eligible participants* for the intervention study, for which power calculations have been carried out (see below). This number of Stage One participants will also provide sufficient variance on all secondary outcome measures to ensure valid correlational analyses between these.

*Recruits to Stage Two must show ‘room for improvement’ on the main primary outcome (i.e. scoring within the lowest tertile on age-standardised measures of reading).

Following the only previous randomized controlled study to assess reading ability, power calculations were performed to estimate likely group sizes ([name] & [name], 2005)). These indicated that with significance set at 5% and power at 90%, groups of 180 (i.e. a total n of 360) would be required, based on our standardized reading change. Other outcomes would have required smaller sample sizes.

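### The protocol names its primary outcome inconsistently (teacher ratings, reading, or an unranked list of four), so the basis for calling the trial positive is not fixed

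*Protocol*

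**What the plan says.** Five sections of the protocol speak to the primary outcome.

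- **Conners Teacher and Parent Ratings** (Assessments and Procedures 2): "Teacher ratings will be the primary outcome measure in both Stage One and Stage Two as this is a school-based study". The scales are described as "yielding age-standardised scores for 7 different sub-scales (6 for teacher ratings) and 7 global scales", and no particular scale is chosen.
- **Sample Size**: recruits to Stage Two must have room to improve "on the main primary outcome (i.e. scoring within the lowest tertile on age-standardised measures of reading"). The calculation is for standardised reading change: "with significance set at 5% and power at 90%, groups of 180 (i.e. a total n of 360) would be required". Other outcomes are said to need fewer children, without figures.
- **Primary outcome** (Statistical Considerations), repeated in Research Questions: "Outcomes assessed will include reading performance, working memory and ADHD-type symptoms (inattention, hyperactivity, impulsivity) as rated by teachers and parents". No ranking is given.
- **Outcome Measures** (Background and Rationale), in the paragraph on cognitive function: "Age-standardised tests of reading performance and working memory will therefore be used as primary outcomes in this study".
- **Primary Endpoint** (Trial Design): the aim is to confirm or refute that DHA "improves behaviour and learning in children aged 7 – 9 years from mainstream schools who are underperforming academically". No instrument is named.

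The reading measure is also labelled in two ways. The Baseline and Post-intervention schedules list "Reading test age", while the BAS II Word reading section, Outcome Measures and Sample Size refer to an age-standardised measure.

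**The concern.** A protocol should let a reader say, before unblinding, which result will decide the trial. Here a statistical analysis plan that followed the Conners section would test teacher ratings. One that followed Sample Size would test reading. One that followed Primary outcome would have four results of equal standing. Each could claim support in the protocol and each would contradict another part of it.

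Two further points follow. Reading is the only outcome with a stated sample size, yet it is not the one that the Conners section calls primary. Parent ratings are supplementary in the Conners section but stand level with teacher ratings in Primary outcome and Research Questions. If the results diverge, for example a benefit on parent ratings and none on reading, the protocol does not say whether DHA has been shown to work.

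**Working it through.** **1. The designations side by side**

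| Section | Reading | Working memory | Teacher ratings | Parent ratings |
|---|---|---|---|---|
| Conners section | not mentioned | not mentioned | the primary measure | also to be collected |
| Sample Size | main primary, sized | not named | not named | not named |
| Primary outcome; Research Questions | listed | listed | listed | listed |
| Outcome Measures (cognitive paragraph) | primary | primary | not covered there | not covered there |
| Primary Endpoint | no measure named | no measure named | no measure named | no measure named |

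The first and second rows conflict as worded. The first and third conflict on whether there is one primary or several, and on the standing of parent ratings.

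**2. The plan's own figure**

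Inputs from Sample Size: 5% significance, 90% power, 180 per group. No effect size, standard deviation or sidedness is given, so 180 can be neither confirmed nor refuted. It can only be solved backwards for a comparison of two means:

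d = √2 × (z for alpha + z for power) / √180

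- Two-sided: √2 × (1.960 + 1.282) / 13.416 = 0.342
- One-sided: √2 × (1.645 + 1.282) / 13.416 = 0.308

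**3. Error rate if any one of four outcomes could carry the trial**

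This assumes a rule that the protocol does not contain: four outcomes (reading, memory, one teacher score, one parent score), each tested two-sided at 5%, with any one sufficient.

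- Independent tests: 1 − 0.95⁴ = 0.185
- Equally correlated tests, by simulation of 400,000 sets of normal statistics: 17.3% at correlation 0.3, 15.6% at 0.5, 13.1% at 0.7
- Counting only false findings in favour of DHA, against a nominal 2.5%: 9.6% if independent, 7.8% at correlation 0.5

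The correlations are assumed; the protocol gives none.

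**4. Power if alpha were split**

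This takes the two-sided d = 0.342 back-solved in step 2 and a Bonferroni split. Power at 180 per group = Φ(3.242 − z for the split alpha), where 3.242 = 1.960 + 1.282.

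| Co-primary outcomes | Alpha each | Power at 180 per group | Per group for 90% |
|---|---|---|---|
| 1 | 0.05 | 90% | 180 |
| 2 | 0.025 | 84.1% | 213 |
| 3 | 0.0167 | 80.2% | 232 |
| 4 | 0.0125 | 77.2% | 245 |

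For four outcomes: 3.242 − 2.498 = 0.744, and Φ(0.744) = 0.772. If the original calculation was one-sided, the figure is Φ(2.926 − 2.241) = Φ(0.685), about 75%. These figures apply to any outcome whose true effect equals the back-solved d. The protocol implies that effect only for reading.

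**The case against.** Much of the apparent conflict softens in context, and some of this stands.

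- The list of reading and working memory in Outcome Measures sits in a paragraph limited to cognitive function, after one on behaviour. It does not exclude behaviour and fits the four-outcome list. This stands, so that section needs aligning but is not a separate contradiction.
- Calling reading the main primary presupposes several primaries with reading in front, which also fits the list. This is fair, but neither Primary outcome nor Research Questions ranks anything.
- The sentence on teacher ratings belongs to the Conners section and contrasts teachers with parents, so it may mean only that teachers take precedence for behaviour. This is plausible, but the wording is not limited to behaviour. Even so read, it clashes with the equal standing of parents in Primary outcome.
- Reading test age appears in schedule lists, and the test is identified elsewhere as age-standardised. This stands: it is a labelling correction.

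A reader might infer that the plan spends 5% on each outcome and so leaves the error rate uncontrolled. The protocol does not say so. The 5% level appears once, for the reading-based sample size, and a multiplicity rule may properly sit in a statistical analysis plan not shown here.

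A reader might also count every Conners score: 6 + 7 = 13 for teachers and 7 + 7 = 14 for parents, with reading and memory making 29, and 1 − 0.95²⁹ = 77%. That is not supported either. Primary outcome and Research Questions restrict behaviour to ADHD-type symptoms, no section makes all 27 Conners scores primary, and independence among scores from the same questionnaires is not credible.

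**Conclusion.** The inconsistency is real and lies within the protocol, so a statistical analysis plan cannot resolve it without contradicting one section or another. What is lost is a fixed basis for declaring the trial positive. It should be corrected because it concerns the decision on which the whole trial turns.

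The size can be given only conditionally: about 18.5% for four independent outcomes, or 13% to 17% at correlations of 0.7 to 0.3, if any one result at 5% were allowed to count. These figures illustrate why the choice matters; they are not the trial's error rate. The power of about 77% under a four-way split rests on the back-solved effect size of about 0.34, two-sided. The contradiction and its remedy do not depend on any of these numbers.

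**What to change.** Name one primary outcome: the change from baseline to 16 weeks in the BAS II word-reading age-standardised score. This is the outcome the trial was sized on, and a change score matches both the sample size statement and the Analysis Plan. Make working memory and one pre-named ADHD-symptom Conners scale for each rater secondary, in a stated order.

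If the sponsor wants several primaries, state the co-primary set explicitly, say whether one or all must succeed, give the alpha rule, and restate the power with its effect size, standard deviation and sidedness.

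Then align Research Questions, Outcome Measures (Background), Primary Endpoint, the Conners section and Primary outcome with that choice. Replace the reading-age label in the Baseline and Post-intervention lists with the same standardised score.

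With a single primary the cost is wording only: alpha stays at 5% and the sample at 180 per group. The downside is that fewer outcomes can be called primary. A co-primary set in which any one result suffices would cost power or children, as in the table above.

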### British Ability Scale (BAS II) Word reading

This is an age standardized single word reading test from the British Ability Scales, normed on UK children It is administered to each child individually, taking only a few minutes to complete.

This kind of reading test was used successfully in the Oxford-Durham trial and was sensitive enough to show significant change over three months.

### British Ability Scale (BAS II) Recall of Digits

This is a widely accepted measure of ‘working memory’ from the British Ability Scales. Again it is age standardized and administered at the individual level.

In the Oxford-Durham study, active treatment was associated with highly significant improvements over placebo in working memory performance, as assessed using this kind of test (, although this was only a secondary outcome., . Working memory problems are common to a wide range of different conditions in which omega-3 supplementation has been found beneficial including dyslexia, dyspraxia, ADHD, depression and age-related cognitive decline. Improvements in working memory are also likely to benefit many different aspects of cognitive performance in the general population.

### Fingerprick blood measures to assess fatty acid status and compliance

A fingerprick blood test will be performed at baseline for children in Stages One and Two andat the end of the study for children in Stage Two, in order toassess levels of fatty acid including docosahexaenoic acid (DHA), arachidonic acid (ARA), and eicosapentaenoic acid (EPA). Analysis of the fatty acids levels will be performed at Martek Biosciences Corporation, and the investigators will remain blinded to these until treatment codes are unlocked.

The fatty acid data will be used to verify compliance and to determine the relationship between levels of fatty acids in the blood and specific endpoints.

This blood test will be optional and will appear as a separate item on the consent form, but every effort will be made to maximize participation.

### Estimate of treatment group

The value of this measure is that it tests that the participants have remained blind to their group allocation.

### Side effects scale

Side effects will be measured post-intervention in all children participating in Stage Two using the Barkley Side Effects Rating Scale (SERS) (Barkley 1990). This scale was designed for use in studies of stimulant medication for ADHD-type symptoms. Based on our own and others’ previous studies, negative side effects are not expected from supplementation with DHA, but we are conscious that few studies specifically ask about these effects, so the use of this scale will redress that omission.

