## Enrolment/ Baseline Assessments

The following baseline measures will be obtained on participating children:

1. Teacher: Conners Teacher Ratings (CTRS-L) (Conners 1997)
2. Parent: Conners Parent Ratings (CPRS-L) (Conners 1997)

Demographics

Child Sleep Habits Questionnaire (CSHQ) (Owens 2000)

3. Child: Word reading and Recall of digits (British Ability Scale - BAS II) (Elliott, 1997)
Fingerprick blood measures to assess fatty acid status and compliance

Sleep measured objectively by actigraph on a 10% subset.

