## Baseline

Confirmation that signed consent forms are in the PIs possession is required before baseline visits to schools will be arranged. The following measures will be administered in the school by the research staff:

Teacher: Conners Teacher Ratings

Child: Reading test age

Working memory digit span test

Fingerprick blood measures to assess compliance

At this point assessment measures will be scored by researchers. Children who meet inclusion criteria for Stage Two will be identified and randomization will be performed by telephone.

The following measures will be collected from parents using Freepost mail services and chased up with telephone calls or visits as required.

Parent: Conners Parent Ratings

Health questionnaire

Demographics

Child Sleep Habits Questionnaire (CSHQ)

On a 10% block random selected subsample of Stage Two participants, we will collect sleep measures objectively by actigraphy. This will require a home visit before supplementation begins to provide the actigraph and explain how to use it, and another home visit to collect it 5 days later.

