### Child Sleep Habits Questionnaire (CSHQ)

The Children’s Sleep Habits Questionnaire (CSHQ) will be completed at baseline by all children participating in Stage One and at post-intervention by all children participating in Stage Two.

This questionnaire, for children aged 4 to 12 years, is designed to screen for the most common sleep problems in that age group. The CSHQ focuses on sleep disorders common to this age group in three domains: Dyssomnias (difficulty getting to sleep or staying asleep, Parasomnias (sleepwalking/talking, night terrors, bedwetting, restless leg syndrome, etc), and Sleep-Disordered Breathing (Owens 2000).

In a 10% subset of children in Stage Two of the study, the duration of night-time sleep and sleep latency will be recorded by additional subjective (sleep diary) and objective means (actigraphy).

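### The side-effects scale is completed only after treatment, so on its own items existing symptoms cannot be told from new ones and the arm comparison gives up some precision

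*Protocol*

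**What the plan says.** Under Side effects scale the Protocol schedules the SERS once: "Side effects will be measured post-intervention in all children participating in Stage Two". The same section explains that few studies ask about such effects, "so the use of this scale will redress that omission". The list under Post-intervention (Stage Two participants only) agrees, placing the SERS among the forms collected from parents by post.

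The scale is in neither baseline list. Enrolment/ Baseline Assessments opens with "The following baseline measures will be obtained on participating children" and names the Conners ratings, demographics, the CSHQ, word reading, recall of digits, the fingerprick blood and actigraphy in a subset. The Baseline section adds a parent "Health questionnaire", whose content is not described and which is not repeated after treatment.

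The other symptom ratings are paired. For the Conners scales, "every effort will be made to ensure that parents also complete ratings pre- and post-treatment". The CSHQ "will be completed at baseline by all children participating in Stage One and at post-intervention by all children participating in Stage Two"; since Stage Two children come from Stage One, each randomised child should have both. No reason is given for treating the SERS differently.

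**The concern.** A symptom score taken once, after 16 weeks, mixes symptoms that began on treatment with those the child already had. The Protocol gives grounds to expect some overlap. It says the scale was built for stimulant studies of ADHD-type symptoms, and its project approval form says underachieving children commonly have behavioural problems too. Without a baseline rating on the same items, no child's record can show which SERS symptoms are new. A chance difference between arms in starting symptoms cannot be corrected on that scale. The Analysis Plan's change-score approach cannot be applied to it either.

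At stake is the usefulness of the one instrument the Protocol brings in to improve the evidence on side effects. An analysis plan cannot repair this later, because a baseline form that was never collected cannot be recovered.

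**Working it through.** **Plan's own figure.** No precision or power is stated for side effects. The only calculation is for reading: "These indicated that with significance set at 5% and power at 90"%, 180 per group are needed, 360 in all. No effect size or SD accompanies it, so 180 cannot be reproduced independently. Back-solving, d = (z for alpha + z for power) × √(2/180):

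- two-sided: (1.960 + 1.282) × 0.1054 = 0.342 SD
- one-sided: (1.645 + 1.282) × 0.1054 = 0.308 SD

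Only the 180 per arm is used below.

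**Inputs.** n = 180 per arm (Protocol, Sample Size). The correlation r between baseline and post-treatment SERS scores is not in the Protocol and is assumed over a range.

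**Score comparison without a baseline, in SD units.**

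- SE = √(2/180) = 0.105
- 95% half-width = 1.96 × 0.105 = 0.207
- difference detectable with 80% power = (1.960 + 0.842) × 0.1054 = 0.295

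**With a baseline SERS as covariate.** The variance is multiplied by 1 − r², the SE by √(1 − r²), and the equivalent unadjusted sample per arm is 180/(1 − r²).

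| r | variance cut | half-width | detectable difference | equivalent n per arm |
|---|---|---|---|---|
| none | – | 0.207 | 0.295 | 180 |
| 0.2 | 4% | 0.202 | 0.289 | 188 |
| 0.3 | 9% | 0.197 | 0.282 | 198 |
| 0.5 | 25% | 0.179 | 0.256 | 240 |
| 0.7 | 49% | 0.148 | 0.211 | 353 |

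A plain change score would not do the same job. Its variance relative to the post-only score is 2(1 − r): 1.4 at r = 0.3, 1.0 at r = 0.5 and 0.6 at r = 0.7. Below r = 0.5 it is worse than having no baseline at all.

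**A single yes/no symptom (illustration).** Assume new onset of 5% against 10%, that any symptom present at baseline persists, and baseline prevalence b in both arms. The post-only proportions are b + (1 − b) × 0.05 and b + (1 − b) × 0.10. With a baseline form, new onset can be compared among the 180 × (1 − b) children per arm who were free of the symptom. Power is by the two-sided 5% normal approximation, Φ[(difference − 1.96 × pooled SE)/unpooled SE].

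| b | post-only proportions | post-only power | power on new onset |
|---|---|---|---|
| 0% | 5.0% v 10.0% | 44% | 44% |
| 10% | 14.5% v 19.0% | 21% | 40% |
| 20% | 24.0% v 28.0% | 14% | 36% |
| 30% | 33.5% v 37.0% | 10% | 32% |

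None of these onset or prevalence figures is in the Protocol. If a symptom is absent at baseline, nothing is lost. The more common and persistent it is, the more a post-only form dilutes the contrast.

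**The case against.** The strongest reply is that this is a preference and not an error. The two places that schedule the SERS agree with each other. The trial has a concurrent, double-blind placebo arm, so background symptoms occur in both arms and the post-treatment difference estimates the treatment effect. That stands: a reader might infer that the side-effect comparison is biased, and the design does not support that reading.

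Four further limits also stand.

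- The SERS is not the only rating taken once. The parents' and teachers' guess of treatment group is post-only by nature, and the health questionnaire is baseline-only. The fair contrast is with the Conners scales and the CSHQ.
- A reader might infer that new symptoms cannot be reported at all. The repeated Conners and CSHQ allow this for behaviour and sleep. The gap is in the SERS items themselves, most clearly any outside those domains. The undescribed health questionnaire may record other symptoms at baseline, but it is not repeated.
- A reader might infer that many children will score on the SERS before treatment. The Protocol does not list the items or give a prevalence. It describes the children as normal apart from reading, and excludes major learning disabilities, medical disorders and medication affecting behaviour. Some overlap is plausible; its extent is unknown.
- The precision gain rests on an assumed r and on an unadjusted comparator. Baseline Conners and CSHQ scores could already serve as covariates, which would leave a smaller extra gain.

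The Protocol also has safety reporting rates checked between centres and gives the steering committee an advisory role on adverse events, but it describes no other tool for collecting side effects.

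These points shrink the concern but do not remove it. A same-scale baseline is the only way to separate old from new symptoms on this scale, and the Protocol already collects parent forms at that time.

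**Conclusion.** The point holds as a cheap improvement. The comparison between arms is unbiased; what is lost is interpretability on the SERS items and some precision. The lost precision is 4% of the variance at r = 0.2, 9% at 0.3, 25% at 0.5 and 49% at 0.7. These figures assume 180 children per arm, a linear adjustment and no other baseline covariates. At r of 0.2 or below the precision argument is minor, but the inability to identify new or worsened symptoms on this scale remains at any r. The primary outcomes and the sample size are untouched.

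**What to change.** Have parents of Stage Two children complete a dated SERS with the other baseline parent forms, before the first capsule. Compare arms on the post-intervention score adjusted for baseline, not on the raw change, and report symptoms that are new or worse since baseline by arm.

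The cost is one more form, in a postal collection already chased by telephone or visit, and one covariate. There are two downsides. If the form goes into the common baseline pack, it also reaches Stage One families whose children are not randomised: up to 600 − 360 = 240. Sending it only once a child is identified for Stage Two avoids this. Forms completed after supplementation starts cannot serve as baseline. The Protocol does not require parent forms to be back before then, so the date on the form is needed to identify them.
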